## Abstract

**Background:**

Normal pressure hydrocephalus (NPH) is a potentially treatable condition causing dementia. Treatment is through insertion of a ‘shunt’, which improves symptoms and prolongs independence, but NPH may be under-treated. Automated brain imaging measures might have potential to identify NPH. Little is known about NPH presentation in memory clinics. This study investigates the period prevalence of NPH and potential use of imaging biomarkers for NPH, especially callosal angle (CA), in detecting NPH in UK memory services.

**Methods:**

This cohort study will use retrospective data from South London and Maudsley Clinical Records Interactive Search and linked datasets. The study population will comprise individuals aged ≥60 years with at least one referral to memory services from 2007–2024 (estimated n>20,000). Automated tools will be used to measure imaging biomarkers using routinely collected brain magnetic resonance imaging scans that are electronically linked to health records in a subset of the population (estimated n>5,000).

**Results:**

We will estimate the period prevalence of NPH in this population. We will evaluate automated measurement tools for imaging features of NPH, describe their distributions, and their variation by covariates (eg. demographics). We hypothesise that people with a diagnosis of NPH will have smaller CA compared to people with a diagnosis of dementia, and that imaging features of NPH will predict future diagnosis of NPH. Depending on our findings, we may undertake more detailed analyses, such as a nested case-control or survival analysis.

**Conclusions:**

This study will give a first understanding of NPH in UK memory services. It will inform future work to improve identification of NPH, for example through a clinical decision support tool. With rising global dementia rates, research into this potentially treatable condition causing dementia is a priority.

## Impact statement

At Spina Bifida Hydrocephalus Information Networking Equality (SHINE) Charity, we support many people with normal pressure hydrocephalus (NPH) who have experienced significant distress, deterioration in health, and loss of independence because of delayed or missed treatment opportunities for NPH. Delays to diagnosis reduce the chance and extent of symptom improvement and, in some cases, mean surgery to place a shunt is no longer an option. This carries a large human and healthcare cost.

Delays in diagnosis are the reason many people with NPH or suspected NPH first contact SHINE for support. We hear their stories of being ‘stuck’ in a slowly moving system, and all the while their abilities are declining. Their carers and loved ones are also profoundly impacted by the consequences of missed or delayed treatment.

Surgery is effective for many with NPH, but early diagnosis is crucial; the sooner a shunt is fitted, the more likely it is to improve physical function and cognition. For patients, it can be transformative: “The most helpful [part of my care] was having the shunt fitted, I think it saved my life” –
*SHINE member*.

Since mind and memory difficulties characterise NPH, memory services could help bridge the gap between symptom onset and shunt treatment. This study will explore the potential of memory services to identify NPH. These services may offer an opportunity to identify NPH sooner. Many patients could stand to benefit from this study and the potential impact of its findings on clinical practice.

## Introduction

### Normal Pressure Hydrocephalus

Normal pressure hydrocephalus (NPH) is a progressive, potentially treatable condition causing dementia. NPH is characterised by gait disturbance, cognitive impairment, and urinary incontinence. NPH involves a build-up of cerebrospinal fluid (CSF) in the brain (‘hydrocephalus’)
^
1
^ among people aged 60 years and above
^
2
^. Idiopathic NPH is thought to have no clear trigger, while secondary NPH is associated with causes such as trauma, meningitis, stroke, and subarachnoid haemorrhage
^
3
^. In clinical practice, decompensated, longstanding congenital hydrocephalus in older age may be indistinguishable from true idiopathic NPH
^
4
^. In this study, we will particularly focus on idiopathic NPH, while recognising the complexity around its nomenclature
^
2
^, and the difficulty in distinguishing between late-decompensating congenital hydrocephalus and true idiopathic cases. In this protocol, we will use the term ‘NPH’ to refer to cases of NPH without an immediate or clear preceding cause.

NPH is diagnosed according to International or Japanese criteria, which are the two major diagnostic systems for NPH
^
3,
5
^. In the latest guidelines
^
5
^, ‘possible’ NPH relies on a clinical history of at least one of cognitive impairment, gait dysfunction, or urinary incontinence, in the absence of a more likely diagnosis, as well as supportive radiological features and investigations. To diagnose ‘probable’ NPH
^
5
^, a normal opening CSF pressure on lumbar puncture, in the presence of either supportive physical examination and imaging findings or objective improvement in gait following removal of a small volume of CSF, known as a ‘tap test’, are also required. ‘Definite’ NPH is diagnosed following a positive response to treatment, which is variably defined. There is ongoing controversy regarding NPH’s definition as a cohesive clinical entity
^
6
^. This is partly due to the confirmation of ‘definite’ NPH relying on treatment response
^
5
^, and the lack of specific pathognomonic pathological findings on post-mortem studies
^
6
^.

Though the pathophysiology of NPH is unknown, there is a growing understanding of the contribution of vascular disease to its aetiology. Alteration in the cerebral vasculature caused by hypertension, a known risk factor for NPH
^
7
^, leads to reduced arterial pulsatility and increased vessel stiffness
^
8
^. This in turn may reduce the clearance of toxins from CSF and glymphatic drainage
^
9
^, leading to the development of NPH. Other proposed mechanisms have included the role of genetically-induced cilia dysfunction in the central nervous system (CNS)
^
10
^. Though there is a paucity of data, previous research has suggested an elevated risk of NPH with white ethnicity, male sex, and higher socioeconomic status
^
11
^. NPH is strongly associated with increasing age
^
12
^. In addition, there are possible associations between NPH and schizophrenia
^
13,
14
^, obstructive sleep apnea
^
15
^, vascular risk factors
^
16
^, and diabetes
^
17
^.

Treatment for NPH is through surgical placement of a tube into the brain to divert CSF to the abdominal cavity, known as a ‘ventriculoperitoneal shunt’ (henceforth referred to as ‘shunt’). Treatment has beneficial effects, with an estimated 82% of people showing improvement
^
18
^. A Cochrane review of randomised-controlled trial (RCT) data of shunt effectiveness for NPH found moderate certainty evidence that treatment improves gait speed (n=116, three RCTs) and functional independence (n=118, three RCTs), with a number needed to treat estimated at 3.4 for the latter outcome
^
19
^. The little available evidence regarding shunting effectiveness for cognitive impairment (n=108, two RCTs) was of very low certainty. However, a meta-analysis of observational data (n=1,059) found significant improvements in global cognition, psychomotor speed, and executive function after shunting. Shunting may also lead to societal and financial benefits. For example, shunting NPH has been estimated as representing a cost saving of approximately 27,921 Euros per patient
^
20
^. One study estimated an incremental cost-effectiveness ratio of approximately £10,000, below the National Institutes for Health and Care Excellence cut-off of £20,000
^
21
^. Despite these benefits, NPH may be under-diagnosed and under-treated, according to multiple community surveys
^
12,
22–
24
^.

### Brain imaging in NPH

Magnetic resonance imaging (MRI) is the preferred modality for assessment of NPH
^
25
^. The classical imaging finding of NPH is enlargement of the ventricles (‘ventriculomegaly’), frequently operationalised as a raised Evans’ Index (EI)
^
26
^. However, this measure varies widely between individuals, is non-specific, and is elevated in a significant proportion (29%) of healthy elderly aged 65–84 years
^
27
^. EI increases with age and with male sex
^
27
^. The presence of disproportionately enlarged subarachnoid space hydrocephalus (DESH), characterised by tight high convexity sulci, enlargement of the Sylvian fissures, and ventriculomegaly, supports the diagnosis of NPH according to guidelines
^
6
^ and predicts response to treatment
^
28
^. In addition, an acute angle at the corpus callosum, widening of the temporal horns, white matter hyperintensities (WMHs), focal bulging of the roof of the lateral ventricles, and focal enlargement of sulci are seen in NPH. These imaging features are indirect markers of communicating hydrocephalus but do not confirm a specific underlying pathophysiological process, and therefore serve as potential indicators rather than definitive signs of NPH. Kockum’s RadScale
^
29
^ is a validated radiological scale incorporating these features that is used to aid pre-operative assessment of possible NPH cases.

### Automated measurement of NPH imaging biomarkers

Due to the importance of imaging features in the diagnosis of NPH, digital imaging technologies could potentially support clinicians in their assessment of possible NPH. In particular, narrowed callosal angle (CA) has been proposed as a potential screening tool for NPH in primary care and non-neurological settings
^
30
^. CA has the advantage of being measurable in both MRI and computed tomography (CT) imaging, even in relatively low-quality scans, and may have high accuracy in identifying NPH. CA has been shown to distinguish NPH from Alzheimer’s dementia (AD) in research populations with high sensitivity (97%) and specificity (88%)
^
31
^. CA can also distinguish NPH from healthy individuals
^
32
^ and clinical mimics such as PSP and vascular dementia (VD) (Area Under Curve= 0.94)
^
33
^. Scaling of such a tool would require automation of CA measurement, which has succeeded in previous studies
^
34,
35
^.

Previous studies have tested CA in research populations
^
32
^, but its ability to distinguish NPH from other conditions in routine clinical imaging has not been investigated. DESH has been found to be strongly associated with the clinical phenotype of NPH including cognitive decline in community and memory clinic populations
^
36–
38
^. Both CA and DESH are predictive of shunt response
^
39
^ and CA has been shown to correlate with DESH
^
40
^, but the clinical correlates of CA have not been explored.

### Memory services

No study has so far explored the role of memory services in assessing people with possible NPH in England, though these are an important source of referrals for NPH clinics
^
41
^. To the best of our knowledge, only one study has examined imaging features of NPH in a memory clinic population
^
38
^.

Electronic health record (EHR) studies of NPH are limited by the possibility of false negatives in recorded diagnoses, due to suspected under-diagnosis of NPH
^
12,
22
^. There is a need to further our understanding of clinical and radiological features suggestive of NPH in clinical populations. In addition, we lack normative data regarding NPH imaging features in clinical populations, which is key when considering the development of screening tools for this condition.

We therefore propose the first study of NPH and its clinical and radiological features in memory clinics in the UK. Little is known about this topic and this study will provide an initial exploration of a neglected area of research. NPH is a rare outcome, with an expected prevalence of 1% in memory services
^
38
^. Due to the uncertainty surrounding recorded diagnosis of NPH, and the frequent co-occurrence of NPH with other neurodegenerative conditions
^
42
^, this study will also examine for the first time whether imaging features of NPH are independent predictors of outcomes, and whether they are associated with prognosis in other diagnoses such as AD and Parkinson’s disease.

Untreated NPH is associated with a higher risk of dementia and death than the general population
^
43
^. If CA or other imaging markers are validated as a reliable measure for this population, these could be developed as automated decision-support tools for NPH, with the potential to benefit both individuals and healthcare systems. Though shunting is not appropriate or effective for all, it could alleviate symptoms and reduce long term costs in a potentially large number of people with cognitive decline. The possibility to prolong independence and potentially delay dementia onset at a time when global dementia cases are unprecedentedly high and set to increase
^
44
^, makes study of NPH a priority.

## Aims and objectives

In this proposal, we aim to investigate the clinical and imaging features of NPH in a memory clinic population. To do this, we will determine the period prevalence of recorded diagnosis and radiological features of NPH in memory services and describe their association with demographic characteristics, risk factors, symptoms, and outcomes, using linked free text notes, hospitalisation, brain imaging, and mortality data. We will evaluate automated tools for measuring CA and other imaging markers on routinely collected brain MRI scans and examine their clinical utility as biomarkers for NPH in this setting. In this memory clinic cohort study, we hypothesise that imaging features of NPH will predict NPH diagnosis. We hypothesise that CA will be smaller among people with a diagnosis of NPH compared to individuals diagnosed with dementia and its subtypes, taking into consideration the caveat that people with NPH may not have a formal diagnosis.

## Methods

### Study population and setting

This study will combine neuroimaging analytics with epidemiological methods. We will assemble a retrospective cohort study using healthcare records from South London and Maudsley (SLaM) memory services over the period 2007–2024. SLaM is one of the largest secondary mental health care providers in the UK, serving over 1.3 million people living in a geographic catchment of four South London boroughs
^
45
^. There are three memory assessment services provided by SLaM to its catchment: Lambeth and Southwark (one combined service), Lewisham, and Croydon. These memory services sit within mental health secondary care services and are predominantly led by psychiatrists, and staffed by a multidisciplinary team including specialist nurses and psychologists. SLaM implemented fully electronic health records for all its services during 2006 with incorporation of legacy data from earlier records systems.

The median age in years of individuals in SLaM (35.1) is comparable to London (35.9) and younger than the general population of England (40.4)
^
46
^. In mid-2023, based on the Office of National Statistics (ONS) estimates, 208,907 people aged 60 years and over lived in boroughs covered by SLaM
^
46
^. Self-described ethnicity in SLaM is comparable to London (see
Table 1), but differs from England as a whole. Compared to the rest of London, Croydon has an average level of income deprivation, while Lambeth, Lewisham, and Southwark are more deprived than average
^
47
^.

**Table 1. T1:** Self-reported ethnicity by geographic area, from the 2023 National Population Survey
^
51
^.

	White	Asian	Black	Other
Lambeth, Southwark, Croydon, and Lewisham	60%	11%	19%	10%
London	60%	18%	12%	10%
England	89%	6%	2%	3%

The study will use routinely collected electronic health record (EHR) data through the Clinical Records Interactive Search (CRIS) platform in SLaM. CRIS has been described previously in detail
^
48
^, but in summary provides researcher access to full, de-identified health records data for all SLaM services within a robust and patient-led governance and ethical framework. No new data will be collected for this study. CRIS contains text-field data on all clinical interactions and assessments in mental health services from before 2006 and has been extensively used for dementia research
^
49,
50
^. CRIS accesses over 500,000 patient records
^
48
^ and is a live data resource, updating against the source EHR every 24 hours. CRIS data have been linked with a range of external sources within a trusted research environment, including all hospitalisations in England (via Hospital Episode Statistics (HES) provided by NHS England) and Office of National Statistics (ONS) mortality and 2011 Census data
^
52
^. Lambeth primary care datanet has additional linkage to CRIS.

CRIS provides linkage to routinely-collected neuroimaging data through the SLaM Image Bank. Full details of the linkage procedure for this have been described elsewhere
^
53
^. The scans used in this study have primarily been carried out on a General Electric (GE) 1.5T HDx model scanner. SLaM images are stored on a secure [name]'s College London server as de-identified raw images, unlinked from clinical information. This server is known as the neuroimaging analytics network. The neuroimaging network is a secure Kings’ College London platform with high performance cluster capacity, which is accessed following appropriate approvals.

Data preparation and curation will be carried out for EHR clinical data and neuroimaging data through separate procedures, as described below.

### Study procedure

**
*Neuroimaging data.*
** We will undertake initial quality control of T1-weighted (T1-w) brain MRIs through visual inspection and using automated quality control tools (eg. MRIQC
^
54
^). We will exclude cases with significant artefact or of insufficient quality to be used in the analysis.

We will use open-access brain segmentation software, SynthSeg
^
55,
56
^, to segment and parcellate brain T1-w MRIs in our population of interest. SynthSeg is a contrast-agnostic machine learning segmentation technique that has been trained on synthetic data and is robust across scan contrasts and resolutions
^
56
^. We chose this tool for its accuracy in the face of variation, which we predict will be high in our routinely-collected clinical imaging dataset.

We will undertake further quality control focussed on SynthSeg output by visually inspecting all participants’ segmentation output to check for gross abnormalities or outliers, and through use of SynthSeg’s in-built quality control function. In a subset of cases, we will manually segment ventricles, using ITK-Snap
^
57
^. Finally, we will compare SynthSeg output results with those of an alternative segmentation technique
^
58
^, using Dice similarity coefficients.

SynthSeg will produce ventricular, CSF, and hippocampal volumes, as well as cortical parcellations. Neuroimaging variables are defined in
Table 2.

**Table 2. T2:** Variable definitions.

Variable name	Definition	Data source	Method of measurement
**Demographics**			
*Age*	Age recorded at index date	CRIS	Medical record
*Sex*	Sex recorded at index date (Male, Female, Other)	CRIS	Medical record
*Ethnicity*	Recorded ethnicity at index date (Black, Asian, White, Other)	CRIS	Self-report in medical record
*Index of Multiple Deprivation (IMD)*	IMD 2019 mean score and decile according to address closest to index date. IMD uses data from seven domains ^ 59 ^: income, employment, education, health, crime, barriers, and environment. These data are applied to Lower Super-Output Areas (LSOAs) of approximately 1,500–2,000 people to measure local geographic socio-economic deprivation. Higher IMD score indicates more deprivation.	ONS	Derived from national Census data and LSOA in CRIS
**Clinical covariates**			
*Diagnosis*	Primary and secondary diagnoses closest to index date, as structured ICD10 codes	CRIS	Medical record
*Health of the Nation Outcome Scale (HoNOS)*	Adjusted total score of HoNOS on or closest to index date. HoNOS ^ 60 ^ is a tool to measure and monitor health and social functioning that is frequently used in UK mental health services. HoNOS gives a score up to four, where the higher score indicates higher severity of a problem, across 12 domains such as behaviour, symptoms, and social functioning.	CRIS	Medical record
*Mini-Mental State Exam (MMSE)*	MMSE total and individual item scores, recorded on or closest to index date. The MMSE ^ 61 ^ is a popular short screening tool for cognitive impairment, comprising 11 questions and a total score of 30, where a lower score indicates worse cognition.	CRIS	Natural Language Processing (NLP) application in medical record
*Addenbrookes’ Cognitive Examination III (ACE-III)*	ACE-III total and individual item scores, recorded on or closest to index date. The ACE-III ^ 62 ^ is a cognitive test involving 21 questions with a total possible score of 100, where a lower score indicates worse cognition. It is used to assess for and characterise cognitive impairment across five cognitive domains: memory, attention, verbal fluency, visuospatial function, and language.	CRIS	Medical record
*Symptoms of NPH*	Ever had a fall, bradykinesia, urinary incontinence before or on or after index date	CRIS	NLP application in medical records and keyword search
*Depression*	Ever had depression symptoms or prescribed antidepressant medication before or on or after index date	CRIS	NLP application in medical records

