**Risk factors for NPH**			
*Hypertension*	Ever had a diagnosis of hypertension or hypertensive disorder or prescribed antihypertensive drugs before or on or up to three months after index date	CRIS	MedCat NLP application and drug search in medical records
*Ischaemic heart disease*	Ever had a diagnosis of ischaemic heart disease before or on or up to three months after index date	CRIS	MedCat NLP application in medical records
*Schizophrenia*	Ever had a diagnosis of schizophreniform disorder before or on or up to three months after index date, as structured ICD10 codes F20–29	CRIS	Medical records
*Diabetes mellitus*	Ever had a diagnosis of diabetes mellitus or prescribed diabetic medication before or on or up to three months after index date	CRIS	MedCat NLP application used on free text in medical records
*Cerebrovascular disease*	Ever had a cerebrovascular accident or diagnosis of transient ischaemic attack or prescribed anticoagulants before or on or up to three months after index date	CRIS	MedCat NLP application used on free text in medical records

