**Outcomes**			
*Diagnosis of NPH*	ICD10 code G91.2 or context-confirmed description of diagnosis of NPH in medical record	CRIS or HES or ONS	Medical record
*Dementia diagnosis*	ICD F00-03 diagnosis on or closest after index date	CRIS or HES or ONS	Medical record
*Cognitive trajectory*	All additional recorded MMSE scores at least three months after index MMSE, until censoring occurs	CRIS	Medical record
*All cause mortality*	First date of death recorded after index date	CRIS	Medical record
*Cause of death*	Recorded primary cause of death based on death certificate	ONS	ONS data
*Hospitalisation profile*	Date and diagnosis associated with hospital episode	HES	Medical record

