### Study design

We will assemble a retrospective cohort study using SLaM’s CRIS data platform. The study population will be all people aged 60 years and above with at least one referral to memory services recorded over the study period 2007–2024. We expect at least 20,000 participants in this cohort. We will extract relevant anonymised retrospective patient data from CRIS for the entirety of the cohort and specify the data extraction date. We will examine CRIS data and use linkage data to HES, ONS, and imaging data.

A subset of this cohort will have linked T1-w, T2-w, and FLAIR brain MRI scans that have been collected as part of routine clinical care over the period 2008–2021. We expect to have at least 5,000 people in this sample, based on the number of scans currently available, however the sample size is subject to change as these datasets are live.

*Inclusion criteria:*

Aged at least 60 years at time of memory clinic referralReferral to memory services, recorded in CRISPeople who are referred but do not attend a review will be included and compared with those who do attend, though they may have limited data

*Exclusion criteria:*

Nil

*Cohort entry date:*

Date of referral to memory service

*Exit from cohort:* Censored at minimum of

DeathIncident NPH diagnosisEnd of study period

*Covariate assessment window:*

Anytime prior to cohort entry date up to three months after date of first face-to-face or virtual review in memory clinic, inclusive

*Primary outcome:* ICD10 code G91.2 recorded in CRIS
*or* HES
*or* ONS,
*or* context-confirmed NPH recorded in CRIS

*Possible secondary outcomes:*

MortalityHospitalisation profileDementia diagnosisCognitive trajectorySymptoms of NPH (eg. falls)

*Exposures:*

CA in degreesVentricular volume in mm
^3^
White matter hyperintensities (WMH) volumesOther brain measures to be determined (TBD)

*Possible covariates:*

AgeSexEthnicityIMDRisk factors for NPHCognitionHealth of the Nation Outcome Score (HoNOS)

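### Table 2 defines NPH symptoms and depression as covariates with no end date, against the protocol's own closed covariate window, so their values depend on length of follow-up

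*Protocol article*

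**What the plan says.** The protocol article gives three different time limits for its covariates.

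- **Table 2, Clinical covariates.** Symptoms of NPH: "Ever had a fall, bradykinesia, urinary incontinence before or on or after index date". Depression: "Ever had depression symptoms or prescribed antidepressant medication before or on or after index date". Neither row has an upper limit.
- **Table 2, Risk factors for NPH.** All five rows carry a limit, for example "Ever had a diagnosis of ischaemic heart disease before or on or up to three months after index date".
- **Study design, covariate assessment window.** "Anytime prior to cohort entry date up to three months after date of first face-to-face or virtual review in memory clinic, inclusive".

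Cohort entry is "Date of referral to memory service". Index date is used throughout Table 2 but is not expressly tied to cohort entry. Study design also lists symptoms of NPH as a possible secondary outcome, and it includes people who were referred but never reviewed, to be compared with those who attended.

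The variables have planned uses. The clinical data text under Study procedure counts symptoms among the clinical covariates. Descriptive analyses will describe imaging features by the covariates in Table 2. Potential further analyses would compare the Table 2 clinical covariates between cases and controls by regression.

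**The concern.** A covariate should be fixed by what was known up to a stated time. An ever/never flag with no end is partly a measure of how long a person was observed and how many notes they generated. Someone referred in 2007 can collect a fall or an antidepressant prescription over many years. Someone referred in 2024 has months at most.

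Three consequences follow where the flags are used:

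- A symptom first noted years after a scan would be described as if it went with that scan.
- Cases and controls observed for different lengths of time would differ in symptoms for that reason alone.
- In a time-to-event model the flag would look protective, because a person must survive long enough to acquire it.

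The study wants to learn how NPH presents in memory clinics, so presenting symptoms need to be kept apart from later ones. The symptoms flag also cannot serve as both covariate and outcome while it is a single undated variable.

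**Working it through.** **Comparison of the text.** The plan states no figure to reproduce, so the first step sets the definitions side by side.

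1. Symptoms and Depression: any time before index, with no end after it.
2. Risk factors: "before or on or up to three months after index date".
3. Study design window: ends three months after first review.

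The missing limit in (1) is not simply the table's style. The risk-factor rows are bounded, and the cognitive trajectory row states its end: "All additional recorded MMSE scores at least three months after index MMSE, until censoring occurs". Windows (2) and (3) also differ from each other. If index date is the referral date, a first review held more than three months after referral lies outside (2) but inside (3). For a person who never attends, (3) has no end date.

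**How strongly the open flag depends on follow-up.** Assume a constant rate r of first recording after index (an assumption; the documents give none). Then P(flagged by time t) = 1 − exp(−r·t).

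- 3 months: r = 0.1 gives 1 − exp(−0.025) = 2.5%; r = 0.3 gives 1 − exp(−0.075) = 7.2%.
- 1 year: 1 − exp(−0.1) = 9.5%; 1 − exp(−0.3) = 25.9%.
- 5 years: 1 − exp(−0.5) = 39.3%; 1 − exp(−1.5) = 77.7%.

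**Effect in a Cox model.** This is a simulation in which the symptom has no effect on death (true hazard ratio 1.0). Every input is assumed:

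- mortality 8–16% per year
- first later recording 2–30% per year, independent of death
- 25–60% already positive before index
- administrative follow-up uniform over 1–17 years
- 2,000 people per data set
- flags stop accruing at exit from the cohort

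Results for the mortality hazard ratio of the flag:

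- Open flag, 12% mortality, 20% recording, 25% positive before index: about 0.35.
- Open flag, 5% recording, 25% positive before index, mortality 8–16%: about 0.59 to 0.67.
- Open flag over the whole grid: about 0.24 to 0.87. The upper end shifts by a few hundredths with the random numbers; a repeat run reached 0.92.
- Flag closed three months after index: about 0.95 to 1.11, scattered around 1.0.

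The bias always runs in the same direction. It is small when later recording is rare and many people are positive at the start, and large when later recording is common.

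**The case against.** The best reply is that the reach is limited, and much of it stands.

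- The Possible covariates list in Study design names neither symptoms nor depression, and the Analysis plan leaves model covariates to causal diagrams. A reader might infer that every mortality, dementia or NPH model is biased. The documents do not support that: no such model is specified with these variables, and the Cox and case-control analyses depend on early findings or on sufficient numbers. Their covariate status rests on the Table 2 heading, the clinical data text (for symptoms) and the case-control plan.
- A reader might also take a single hazard ratio such as 0.35 as the size of the problem. It is one point in an assumed range, and it is the coefficient of the flag, not of an imaging exposure. With a null exposure moderately related to symptoms (0.3 on the log-odds and log-rate scale per SD, again assumed), adjusting for the open flag moved the exposure hazard ratio only to about 1.0 to 1.1 per SD.
- It is tempting to say that symptoms recorded after an NPH diagnosis would predict it. Cohort exit at incident NPH diagnosis may prevent this, although the two rows do not say that it caps them. Records after the window but before diagnosis would still count. The simulation stops flags at exit, and the bias remains.
- The outcome role of symptoms may explain the word 'after' in that row. It does not explain the depression row, which has no outcome role.
- The protocol already accepts that non-attenders may have limited data and plans checks for systematic differences in data collection. Neither supplies an end date for their window.

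None of this removes the conflict between Table 2 and Study design.

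**Conclusion.** The inconsistency is explicit and should be fixed. As Table 2 stands, symptom and depression status depends on length of observation and can draw on events after the scan or outcome. This can distort the description of imaging features by covariates, the possible nested case-control comparison, and any Cox model that includes either variable. In the first two the routes are unequal ascertainment and reverse timing; in the third it is immortal time. Period prevalence, validation of the automated CA measure, and the unadjusted CA comparison with its sample size do not use these variables and are unaffected.

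The size is illustrative only: a mortality hazard ratio of about 0.24 to 0.87 for the open flag when the truth is 1.0, against about 1.0 for a flag closed at three months. The rates behind it are assumptions. The closed flag was modelled from index date, because the documents give no time from referral to first review. Because the affected analyses are descriptive or conditional, this is a should-fix point and not a threat to the study's main results.

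**What to change.** 1. In Table 2, restrict the covariate versions of Symptoms of NPH and Depression to the covariate assessment window in Study design.
2. Use that same window for the five risk-factor rows, and state that index date is the cohort entry date. Keeping the anchor at first review matters: closing the window three months after referral could leave out the assessment at which symptoms are recorded.
3. Define symptoms first recorded after the window as a separate, dated secondary outcome among people free of that symptom within it.
4. For non-attenders, set a window end that does not depend on a review. In the comparison of attenders with non-attenders, use a window of equal length for both groups.

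The cost is wording and date filters, with no new data. Somewhat fewer people will be flagged positive. It is best settled before extraction.
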